##### Health literacy

To examine bivariate associations between health literacy and the participation rate and between FCCHL and process measures, independent *t* tests and chi-square statistics will be used.

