##### SES-sensitive implementation strategy

The SES-sensitive implementation strategy will encompass all the topics described in the regular implementation strategy, but will be tailored to match the needs of the lower-SES target group.

The GP nurses will receive a 3-h training (instead of a 2-h training), and follow-up meeting of 1.5 h (approximately 2 months after the training visit) in which extra elements of the SES-sensitive implementation strategy will be addressed. This additional section of the training was developed in collaboration with a representative of the Dutch Centre of Expertise on Health Disparities (Pharos). An important component is the recognition and guidance of lower-SES patients who might benefit from the online CDMIs. GP nurses will be taught about the concept and consequences of health-literacy skills and ways to recognise and align with the needs of patients with a lower SES or low/limited health-literacy skills. They will practice with methods to provide support to patients with lower SES or health-literacy skills (e.g. easier language and communication, teach-back method). They will also be strongly advised to provide a more directive approach to guiding patients and encouraging them to use the CDMIs. Practical tips will be given to do this, such as: not immediately offering the online CDMIs during the first visit, but after trust and alliance have been established, seeking contact more often (face-to-face, by telephone or monitoring system) to provide guidance, helping patients create an account, indicating which exercises the patient should do (an overview of exercises and suggestions is given in the manual), doing the online exercises with patients during face-to-face sessions before doing them alone (modelling), focussing on one or a few exercises to reduce the chance of experiencing failure, using appropriate language and checking whether information is understood (e.g. using the teach-back method).

The GP nurses in this condition will also have access to a helpdesk service, at least two implementation team meetings and ongoing communication activities from the research teams, but special attention will be paid to the lower-SES target group in all these actions.

Additional elements of the SES-sensitive implementation strategy aimed at the patients are:

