### Outcome measures

#### Primary outcome

The (difference in the) participation rate of patients with a lower SES in the CDMIs is the primary outcome. Participation is defined as participating in at least one face-to-face session with a GP nurse (as registered by the GP nurse) and engaging with at least two exercises in the online CDMIs (as determined with the user data of the online CDMIs). It is hypothesised that in the SES-sensitive implementation strategy arm of the trial the participation rate of lower-SES patients will be significantly higher than in the regular implementation strategy arm. This outcome requires an operational definition of SES, but SES can be defined in various ways. Indicators that are commonly used are education, income and work status/occupation [31–35]. Education is a widely used indicator, especially in the Netherlands, and has some advantages over the other two indicators [36–38]. First, the level of education is generally stable after early adulthood, whereas work status and level of income fluctuate more. Second, in general, respondents are willing to report their level of education, while respondents might be unwilling to disclose or even misstate the level of their income [38, 39]. For these reasons, education will be the main indicator of lower SES in this study. In addition to education level, income, work status and status level of the neighbourhood will be taken into account because these indicators cover different dimensions of SES and are, although interrelated, not interchangeable with education [33, 34].

Therefore, in this study, a lower SES will be defined as:
The highest completed educational level is intermediate vocational education (i.e. between lower and higher vocational education, in Dutch: MBO in Dutch: MBO) or lower, and/orThe respondent is unemployed (looking for work) and lives in a neighbourhood with a negative status level score, and/or:The total gross family income of the respondent is below the social minimum income in the Netherlands (per July 2017), and lives in a neighbourhood with a negative status score

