#### Implementation-related factors

##### Health literacy

To increase the uptake of self-management interventions among people with a lower SES it may be important to take their health-literacy skills into account. Health-literacy skills, defined by the WHO as ‘the cognitive and social skills which determine the *motivation* and *ability* of individuals *to gain access to, understand and use information* in ways to promote and maintain good health’, play a crucial part in empowering people to use self-management interventions [23, 46]. Low or limited health-literacy skills are more prevalent among vulnerable groups, including people with a low education and a low income [22, 47, 48]. Examples of ways to pay attention to health-literacy skills in the implementation of interventions are: increasing the skills of health care providers to recognise low health-literacy skills, adapting communication into an easier understandable way, and helping people navigate through an intervention [49].

Health literacy will be assessed using the 14-item Dutch Functional Communicative and Critical Health Literacy Scale (FCCHL) [50, 51]. The items are scored on a 4-point scale (1 = never to 4 = always). Items can be summed and divided by the total number of items to obtain a total score ranging from 1 to 4, with higher scores indicating higher levels of health literacy.

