##### Fidelity and adherence

Adherence to the intervention by patients will be assessed with user data that are collected in the online CDMI system (i.e. the number of number of completed exercises and diary/monitor entries). The fidelity of the GP nurse to the intervention will be assessed by questioning GP nurses in the follow-up questionnaires about the guidance that they have given (e.g. the rate to which they recommended exercises, the type of exercises recommended, the intensity of the guidance). Furthermore, GP nurses will be asked to report per patient about the number of face-to-face consultations. These data will also be used to provide some insight into the costs of the intervention. For costing we shall make use of the pertinent Dutch guideline for economic evaluation and rely on the standard cost prices reported therein. These will be indexed to the study’s reference year 2017. The user data of the monitoring system will be used to evaluate the use of this tool by GP nurses.

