### Sample size calculation

The sample size is based on the main outcome, namely participation rate of patients with a lower SES. This is defined as participating in at least one face-to-face session with a GP nurse and completing two exercises in the online CDMIs (see above). We expect a (base) participation rate of 18% with the regular implementation strategy. Due to a paucity of studies about online psychological interventions offered and guided by primary care professionals, this percentage is based on previous (baseline) participation rates of lower-educated people in studies of online self-help interventions for depression [18, 20]. This percentage also takes into account that our definition of participation entails more than just starting with the intervention/trial and that attrition in e-health can be related to indicators of lower SES [9]. We aim to double the participation rate of lower-SES patients to 36% by using the SES-sensitive implementation strategy; a smaller effect was not deemed to be relevant. As far as we know, there is no empirical evidence that might support this doubling; however, our rationale is that with specific training and specific materials this percentage of participating lower-SES patients can be reached. The difference between these fractions (0.18 vs. 0.36) will be tested at a two-sided significance level of 5% and a power of 80%. Accounting for the clustering in the data with six patients on average per GP nurse (range 2–14 patients) and an intraclass correlation of 0.02, we need *n* = 114 patients in each condition (in 19 GP nurses per condition) or 228 participants in total. This normative sample size calculation was performed in Stata version 14.2 statistical software package using the clustersampsi-procedure, taking into account the mean cluster size, cluster size variation and the intraclass correlation [53]. The intraclass correlation value of 0.02 was based on the Hospital Anxiety and Depression Scale (HADS)-depression scores in the primary care setting as reported by Adams and colleagues (2004), Table 5 [54].

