#### Additional analyses

Demographic factors will be used to describe the characteristics of the study sample at baseline. Attrition analysis will be conducted by comparing demographic characteristics of the patients who participated in the blended online CDMIs vs. the non-participants. Also, demographic characteristics and psychological complaint outcome variables of the participants who completed the follow-up questionnaires with those who did not complete these assessments will also be compared. For the purpose of attrition analysis, differences between the groups will be tested using independent *t* tests and chi-square statistics.

Because (lower) SES can be defined in various ways and there is no clear common definition, we will conduct additional sensitivity analyses with (lower) SES as outcome defined in other ways. For example, we will use a lower cut-off for educational level (MBO4 and/or MBO1 instead of MBO-4) to define lower SES. We will also examine the use of more than two exercises as an alternative in the definition of participation.

Exploratory analyses, with an interaction term, will be conducted to examine whether health literacy modifies the effect of implementation strategy on participation of lower SES patients. We will also explore the user data of the participants to see if lower SES patients (in both group) use the CDMIs differently than higher-SES patients.

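### The bivariate tests planned for health literacy cannot adjust for arm, so the association with participation may partly be an arm effect; they also fit count process measures poorly

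*Protocol article*

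**What the plan says.** All references are to the protocol article.

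- **Planned tests.** Statistical analysis, Health literacy: "To examine bivariate associations between health literacy and the participation rate and between FCCHL and process measures, independent" t tests and chi-square statistics are the named methods. No arm, nurse or practice term is mentioned.
- **Health-literacy score.** Implementation-related factors, Health literacy: the FCCHL has 14 items. "Items can be summed and divided by the total number of items to obtain a total score ranging from 1 to 4". No cut-off is given.
- **Participation.** Primary outcome: this is a yes/no variable. "Participation is defined as participating in at least one face-to-face session with a GP nurse", together with use of at least two online exercises.
- **Process measures.** Fidelity and adherence: adherence is taken from user data, the "number of completed exercises and diary/monitor entries". Nurses also report the number of consultations per patient. These are counts.
- **What differs by arm.** In the SES-sensitive arm only, nurses are taught "ways to recognise and align with the needs of patients with a lower SES or low/limited health-literacy skills", and are advised to make contact more often and to practise exercises with the patient. Design says nurses cannot be blinded. Eligibility criteria and recruitment says they recruit under the strategy of their own arm.
- **Other analyses.** The primary outcome and the complaint and well-being outcomes use mixed models that allow for clustering. Additional analyses adds an exploratory interaction of health literacy with strategy, for participation of lower-SES patients.

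**The concern.** A two-variable test of literacy against participation is open to confounding by arm if arm is linked to both variables. The link with participation is what the trial expects to find. The link with literacy is plausible. Nurses who know their allocation choose whom to approach, and one group of nurses has been trained to notice patients with limited literacy. Randomising nurses does not protect the case mix of patients recruited afterwards. The same holds for process measures, because the SES-sensitive strategy is built to raise contact and exercise use.

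If both links exist, the planned test can report a literacy association that arises from arm alone. It can also weaken a real one: if the SES-sensitive arm recruits patients of lower literacy and gets more of them to participate, a true tendency of more literate patients to participate more is pulled towards zero.

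There is also a problem of fit. FCCHL is a score and the adherence measures are counts. Neither a two-group t test nor a chi-square can relate a score to a count unless one of them is first divided into categories, and the article defines no categories.

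**Working it through.** **The plan's own figure.** The Health literacy paragraph gives no number, so the inputs come from Sample size calculation: "The difference between these fractions (0.18 vs. 0.36) will be tested at a two-sided significance level of 5% and a power of 80" per cent, six patients per nurse on average (range 2 to 14), intraclass correlation 0.02, and 114 patients (19 nurses) per arm. The standard two-proportion formula gives 95 per arm before clustering. With equal clusters the design effect is 1 + (6 − 1) × 0.02 = 1.10, and 95 × 1.10 = 104.5, or 18 nurses (108 patients). Using t quantiles on 2(k − 1) degrees of freedom for k nurses per arm, the pooled-variance formula gives 19 nurses (114 patients) for an assumed coefficient of variation of cluster size of 0 to 0.5. The stated figure is therefore reproduced.

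**Bias from omitting arm.** Assume no association between FCCHL and participation within either arm, FCCHL recorded for all 228 patients, and 18% and 36% participation among all patients analysed.

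- Participants: 114 × 0.18 + 114 × 0.36 = 61.6. Non-participants: 228 − 61.6 = 166.4.
- Share of participants from the SES-sensitive arm: 0.36/(0.18 + 0.36) = 0.667.
- Share of non-participants from that arm: 0.64/(0.82 + 0.64) = 0.438.
- Spurious difference in mean FCCHL = (0.667 − 0.438) × shift ≈ 0.228 × shift (unrounded shares), where the shift is the between-arm difference in SD units.
- Standard error = √(1/61.6 + 1/166.4) = 0.149 SD.
- Rejection rate ≈ Φ(−1.96 + |bias|/0.149) + Φ(−1.96 − |bias|/0.149).

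The formula was checked by simulation: 38 nurses with 6 patients each, intraclass correlation 0.02 for both variables, 4,000 runs per setting.

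| Assumed shift (SD) | Spurious difference (SD) | Rejection, formula | Rejection, simulated t test | Simulated, with arm term |
|---|---|---|---|---|
| 0 | 0 | 5% | 5.0% | 5.1% |
| −0.2 | −0.05 | 6% | 6.0% | 4.9% |
| −0.3 | −0.07 | 7% | 8.2% | 5.4% |
| −0.5 | −0.11 | 12% | 11.6% | 5.4% |

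Both links are needed. With a shift of −0.5 SD but 27% participation in both arms, the unadjusted test rejects 5.1% of the time.

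**Nurse clustering alone.** With no shift, the unadjusted t test rejects 5.0% of the time at an intraclass correlation of 0.02 and 5.2% at 0.05. Leaving out the nurse has almost no effect at the protocol's value.

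**Fit of test to variables.**

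| Pair | Types | Does a t test or chi-square fit? |
|---|---|---|
| FCCHL and participation | score, yes/no | Yes: the t test compares mean FCCHL between participants and non-participants, uncut |
| FCCHL and exercises, diary entries or consultations | score, count | Only if one of the two is cut into groups |

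**The case against.** The strongest reply is that the analysis is called bivariate. It is secondary, has no stated hypothesis or power, and reads as descriptive. The size of the confounding rests on a between-arm shift that the documents do not give: there is no FCCHL standard deviation, distribution or expected difference. Even at 0.5 SD the spurious difference of 0.11 SD stays below one standard error. The article also already plans a model containing both health literacy and strategy. All of this is fair, and it limits the point to a minor, conditional one. It does not remove it: the tests are named rather than left open, they cannot take an arm term, and the planned interaction model is exploratory, confined to participation of lower-SES patients, and does not cover process measures.

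Some stronger readings are tempting but not supported:

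- A reader might infer that the plan cuts FCCHL into groups throughout and so discards information (a median split would keep 2/π = 0.64). No split is stated, and for participation none is needed.
- A reader might take the association to be confounded by arm as a fact. The documents make this plausible only.
- A reader might take it that the two arms are pooled. That is the natural reading of a bivariate test, but the text does not say so.
- A reader might treat the omitted nurse effect as serious. At an intraclass correlation of 0.02 it is negligible.
- A reader might extend the point to the attrition comparisons, where "differences between the groups will be tested using independent" t tests and chi-square. Those describe who took part and who completed follow-up, and nothing in the documents shows that they need arm adjustment.

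**Conclusion.** The point holds in limited form. The named tests cannot separate a literacy association from an arm effect, and the trial's recruitment after allocation and one-sided literacy training make such mixing possible. Type I error would be about 6% to 12% for assumed shifts of 0.2 to 0.5 SD, against about 5% with an arm term or with no shift. These figures assume that the 18% and 36% rates, which the protocol states for lower-SES patients, apply to everyone analysed; the paragraph names no analysis population. The dilution of a real association is argued by direction only and was not quantified. Separately, the tests do not suit FCCHL against counts; that objection does not reach FCCHL by participation. Severity is minor, and the primary comparison is unaffected.

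**What to change.** In the Health literacy paragraph of the statistical analysis, make regression the method for both associations:

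- **Participation:** mixed-effects logistic regression on continuous FCCHL, with arm as a fixed effect and GP nurse as a random intercept.
- **Process measures:** a mixed linear or mixed count model, according to the measure, with the same terms.
- **t tests and chi-square:** keep them as descriptive summaries only. If FCCHL or a count is grouped for a chi-square, state the grouping in advance.

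The nurse intercept changes little numerically but respects the unit of randomisation. The cost is a few lines of wording here or in the statistical analysis plan. The data are already to be collected, and the participation model is the planned primary model with one covariate added.

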##### Costs

In the context of this implementation study, the cost analysis will have to be very simple and descriptive in nature. Our cost analysis will be restricted to just mapping (and quantifying) the extra financial costs for rolling out the SES-sensitive implementation strategy as compared to opting for the regular implementation strategy.

##### Process indicators of implementation

Descriptive statistics will be obtained on satisfaction, feasibility, fidelity and adherence with the intervention. In line with the UTAUT model, relationships between performance expectancy, effort expectancy, social influence, facilitating conditions, and behavioural intention to use the intervention will be explored in regression models. Interviews with GP nurses and patients will be transcribed verbatim. The transcripts will be analysed by coding the texts using qualitative analysis software (MaxQDA) and themes concerning potential improvements to the blended online CDMIs and impeding and facilitating factors for (sustained) implementation will be identified and described.

#### Additional analyses

Demographic factors will be used to describe the characteristics of the study sample at baseline. Attrition analysis will be conducted by comparing demographic characteristics of the patients who participated in the blended online CDMIs vs. the non-participants. Also, demographic characteristics and psychological complaint outcome variables of the participants who completed the follow-up questionnaires with those who did not complete these assessments will also be compared. For the purpose of attrition analysis, differences between the groups will be tested using independent *t* tests and chi-square statistics.

Because (lower) SES can be defined in various ways and there is no clear common definition, we will conduct additional sensitivity analyses with (lower) SES as outcome defined in other ways. For example, we will use a lower cut-off for educational level (MBO4 and/or MBO1 instead of MBO-4) to define lower SES. We will also examine the use of more than two exercises as an alternative in the definition of participation.

Exploratory analyses, with an interaction term, will be conducted to examine whether health literacy modifies the effect of implementation strategy on participation of lower SES patients. We will also explore the user data of the participants to see if lower SES patients (in both group) use the CDMIs differently than higher-SES patients.

## Discussion

A report on prevention in Dutch health care [55] suggested that integrating preventive e-health within primary care would be a necessary and important precondition to increase the reach of depression prevention. It explicitly suggests that the GP and the GP nurse should expand their therapeutic arsenal by offering blended care, i.e. expand their face-to-face care with Internet modules. Exactly how this should be done and which implementation strategies would be best is currently unclear. This is particularly relevant for lower SES groups because of their lower participation rate in e-health interventions, despite their elevated risk developing mental health disorders [8]. There is a clear need to develop a dedicated implementation strategy to implement effective e-health for depressive complaints, in order to increase their reach, especially among disadvantaged and lower-SES groups. It is, therefore, also important to empirically test whether a dedicated SES-sensitive implementation strategy will actually increase the participation rate of this group of patients. A strength of our study is that a regular and a dedicated implementation strategy will be compared in a randomised implementation trial. As noted before, defining SES in general and lower SES in particular is complex. We will, therefore, use a composite measure to define lower SES which takes various factors (i.e. education, work status, income, and the SES of the neighbourhood) into account to tackle this issue. Moreover, in this study we focus on lower SES (i.e. including medium education levels) as opposed to only low SES due to the fact that, at the moment, especially highly educated individuals seem to use e-health. For this reason, our primary focus is on improving participation rates in a broader group of lower SES patients. However, we have planned sensitivity analyses to examine different operational definitions of low(er) SES, including using a lower cut-off for education level than in the primary analysis, in order to determine the impact of the implementation strategies when other definitions of low SES are used.

In conclusion, this study should contribute to our knowledge of reaching lower SES groups with an evidence-based brief and complaint-specific blended approach for depressive complaints in primary care. It should also further our knowledge on successful strategies to implement online depression prevention in primary care in general.

